## Abstract

**Background:**

Acute kidney injury (AKI) is frequent and associated with poor outcome in intensive care unit (ICU) patients. Besides the association with short- and long-term mortality, the increased risk of chronic kidney disease (CKD) has been recently highlighted in non-ICU patients. This study aims to describe the incidence and determinants of CKD after AKI and to develop a prediction score for CKD in ICU patients.

**Methods:**

Prospective multicenter (*n* = 17) observational study included 1200 ICU patients who suffered from AKI (defined by an AKIN stage ≥ 1) during their ICU stay and were discharged alive from ICU. Preexisting end-stage renal disease (ESRD) and immunosuppressant treatments are the main exclusion criteria. Patients will be monitored by a nephrologist at day 90 and every year for 3 years. The main outcome is the occurrence of CKD defined by a creatinine-based estimated glomerular filtration rate (eGFR) lower than 60 mL/min/1.73 m^2^ or renal replacement therapy for ESRD in patients whose eGFR will be normalized (≥ 60 mL/min/1.73 m^2^) at day 90. Secondary outcomes include albuminuria changes, eGFR decline slope and ESRD risk in patients with preexisting CKD, cardiovascular and thromboembolic events and health-related quality of life.

**Discussion:**

This is the first study prospectively investigating kidney function evolution in ICU patients who suffered from AKI. Albuminuria and eGFR monitoring will allow to identify ICU patients at risk of CKD who may benefit from close surveillance after recovering from AKI. Major patient and AKI-related determinants will be tested to develop a prediction score for CKD in this population.

*Trial registration* ClinicalTrials.gov, NCT03282409. Registered on September 14, 2017

## Background

 Acute kidney injury (AKI) occurs very frequently in patients admitted to an intensive care unit (ICU). The prevalence of AKI in ICU patients has been estimated between 5 and 15% [1–3]. It is strongly and independently associated with short- and long-term mortality [4]. While acute tubular necrosis is the most frequently reported cause of AKI in ICU patients, numerous pathological patterns have been observed in autopsy of kidneys in patients who died in the ICU following a septic shock [5]. This highlights the complexity of AKI in ICU, related to many harmful factors from ischemia–reperfusion lesions to sepsis-specific injuries. This may explain the association with AKI occurrence in the ICU and long-term mortality as some of these injuries are not as able to regenerate as tubular cells [3]. Moreover, endothelial dysfunction may be a worsening factor impacting long-term renal recovery and so the occurrence of chronic kidney disease.

Besides an association between AKI occurrence and long-term arterial hypertension, AKI has also been associated with chronic kidney disease (CKD), even if glomerular filtration rate (GFR) rose back to normal range [6, 7]. However, most of these data come from administrative registries and mostly include non-ICU patients. In the ICU setting, Wald et al. [8] reported an incidence of end-stage renal disease (ESRD) of 2.63 and 0.91 cases per 100 ICU person-year in patients with AKI requiring dialysis during the ICU stay, and in matched controls without AKI, respectively. While it is well recognized that an early management of CKD patients may slow GFR decline, the identification of AKI patients at risk to develop CKD is uneasy.

Thus, we aim to develop a prediction score for CKD in patients who suffered from AKI during their ICU stay and were discharged alive using a prospective multicenter observational study.

## Methods/design

### Design and setting

The prediction of chronic kidney disease after acute kidney injury in the intensive care unit (PREDICT) study is a multicenter observational prospective study promoted by the Assistance Publique—Hôpitaux de Paris. The study aims to evaluate factors associated with CKD risk in patients discharged alive from ICU and who suffered from AKI during ICU stay. The study was designed by both the medico-surgical intensive care unit and the department of clinical research and public health of Ambroise Paré Hospital (Boulogne-Billancourt, France) and the INSERM (French National Institute of Medical Research) Unit 1018 (Villejuif, France).

Patients who comply with the inclusion criteria will be monitored by a nephrologist at day 90 after ICU discharge and annually thereafter during 3 years: creatinine-based GFR estimation (eGFR), albuminuria measurement, cardiovascular events as well as health-related quality of life will be collected at each time point as shown in the Standard Protocol Items: Recommendations for Interventional Trials (SPIRIT) 2013 diagram (Fig. 1).

**Fig. 1 Fig1:**
[figure not shown]
SPIRIT diagram

### Ethical considerations

This study follows the principles of the Helsinki Declaration 2008. The whole protocol has been reviewed and approved by the *Comité de Protection des Personnes*—*Sud*-*Est III* (no. 2017-053B).

### Registration

The study is registered on Clinical Trials (NCT03282409) and on the European Clinical Trials Database (*EudraCT 2017*-*A02649*-*44*).

### Participants

The study will enroll adults (18 years or older) discharged alive from ICU and who suffered from AKI during ICU stay. Participants will be eligible if they meet the acute kidney injury network (AKIN) classification stage 1 or higher [9]. All patients will have to be able to read and understand the patient information form and provide written informed consent. Patients will not be eligible for enrollment if (1) they suffer ESRD (defined by an eGFR below 15 mL/min/1.73 m^2^ or renal replacement therapy, i.e., dialysis or renal transplantation) before the index hospitalization, (2) they require renal replacement therapy at ICU discharge, (3) if they were prescribed immunosuppressive agents before index hospitalization or (4) there was no extra-renal failure at the time of acute kidney injury (defined by a SOFA score without the renal component equal to 0). Other exclusion criteria are expected life expectancy less than 90 days, inability to perform follow-up (homeless patients, main address far away from the nephrology center, etc.), pregnancy, privation of liberty by administrative or judicial decision, no affiliation to the national social security scheme and refusal to participate in the study.

### Recruitment, inclusion and consent

Patients will be recruited at ICU discharge. After a first screening with regard to the inclusion and exclusion criteria, patients who fulfill the inclusion criteria and are willing to participate will be included in the study after providing written informed consent. Patients will be recruited from 17 ICU (15 in the Greater Paris area, 1 in Clermont-Ferrand and 1 in Amiens) and monitored in 10 nephrology centers.

### Confidentiality

All original records will be kept on file at the trial sites or the coordinating data center for 15 years. The frozen trial database file will be kept on file for 15 years.

### Sample size

The sample size was calculated based on the primary outcome, namely the occurrence of de novo CKD at 3 years. Assuming an attrition bias of 10% and a competing risk of death of 20%, we calculated that 1200 patients fulfilling the inclusion criteria should be included according to the following distribution: 700 AKI patients who would fully recover kidney function at ICU discharge, 150 with impaired kidney function at ICU discharge and 350 with preexisting CKD. According to epidemiological data provided by the multicenter prospective observational study CUB-REA [10] and assuming an inclusion rate of 50% of the patients fulfilling the inclusion criteria, we estimated that the inclusion pace could be 5 patients/center/month leading to study completion within 24 months.

### Nephrologist active follow-up

Every patient will be monitored by a nephrologist at day 90 after ICU discharge and then every year for 3 years. As shown in the SPIRIT diagram, CKD will be evaluated by creatinine-based eGFR and urinary albumin (protein)-to-creatinine ratio. Cardiovascular and thromboembolic events will be collected as well as health-related quality of life.

### Primary and secondary outcomes

The main outcome of the study will be the incidence of CKD defined by an eGFR lower than 60 mL/min/1.73 m^2^ for at least 3 months or chronic dialysis initiation or renal transplantation, as previously published (KDIGO) in patients who recovered kidney function at day 90, defined by an eGFR ≥ 60 mL/min/1.73 m^2^.

The secondary outcomes will include:CKD progression defined by an eGFR decline greater than 30% at 3 years or the occurrence of ESRD (defined by an eGFR lower than 15 mL/min/1.73 m^2^ or chronic dialysis initiation or renal transplantation) in patients with preexisting CKDEvolution of urinary protein-to-creatinine ratio (mg/mmol)Prevalence of patients discharged from ICU with end-stage renal diseaseOccurrence of cardiovascular (acute coronary syndrome, ischemic stroke, peripheral artery disease, ventricular rhythm disorders, sudden death) and/or thromboembolic (deep-vein thrombosis or pulmonary embolism) eventsAll-cause and cardiovascular long-term mortalityHealth-related quality of life using the KDQOL-SF-12 [11] and the EQ-5D-5L [12] questionnaires.

### Biological sampling

We plan to sample 10 mL of plasma at inclusion. This biobank will be stored at *the Centre de Ressources Biologiques* (Hôpital Ambroise Paré, APHP) and will be used to assess the association between biomarkers of kidney injury and long-term outcomes.

### Pre-planned ancillary analysis: 10-year follow-up

We plan to extend patient follow-up up to 10 years through record linkage between the PREDICT database and the following datasets:The national Renal Epidemiology and Information Network (REIN) registry to identify ESRD events (dialysis and kidney transplantation) [13]The national death registry (RNIPP, Registre national d’identité des personnes physiques) to assess vital status and identify cause(s) of death.The national health insurance information system (SNIIR-AM) to collect data about patient use of health resources.

Patient consent for this ancillary study will be requested at inclusion in the main study.

### Data collection, monitoring and data analysis

During the visits, data will be collected in an electronic case report form (eCRF) using CleanWEB software (TéléMédecine^®^, Boulogne, France). This data management system allows direct data entry. Data entry will be monitored by an independent researcher according to a predefined monitoring plan. Patient confidentiality will be ensured by using identification numbers.

Patient baseline characteristics will be compared between AKIN categories at inclusion using analysis of variance or Mann–Whitney test and Pearson’s Chi-square test for continuous and categorical data, respectively. Factors associated with main outcome will be evaluated using a competing risk survival analysis. Factors associated with the main outcome in univariate analysis with a *p* value lower than 0.10 will be included in the multivariate model. Clinically relevant interactions will be studied (especially with age, gender and preexisting diabetes). Factors associated with long-term mortality will be evaluated using the same methodology.

Yearly eGFR assessment will allow to describe the evolution of GFR over time and the evaluation of factors associated with eGFR decline. This analysis will be performed using mixed models with random intercepts and slopes.

The score aiming at predicting the occurrence of CKD at 3 years will be built as follows: (1) evaluation of factors associated with the main outcome using competing risk analysis, (2) assessment of the selection of the variables using the least absolute shrinkage and selection operator (LASSO) method, (3) evaluation of score performance, (4) assessment of the internal validity using bootstrapping. Such a score will be developed using two-thirds of the entire cohort and validated (external validation) using the remaining one-third.

The findings of this study will be published in national and international journals.

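### Mann–Whitney, a two-group test, is named for baseline comparisons across AKIN categories, where Kruskal–Wallis is needed (minor)

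*Protocol article*

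**What the plan says.** The section on data collection, monitoring and data analysis states that baseline characteristics will be "compared between AKIN categories at inclusion using analysis of variance or Mann–Whitney test" when continuous, and by Pearson's chi-square test when categorical. The section on participants sets the entry level: "Participants will be eligible if they meet the acute kidney injury network (AKIN) classification stage 1 or higher". Neither section says how many AKIN categories will be compared, whether stages will be merged, or whether pairwise comparisons with adjustment are meant.

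The same analysis section continues: "Factors associated with main outcome will be evaluated using a competing risk survival analysis". It then describes univariate screening at p < 0.10, after which the retained factors "will be included in the multivariate model", and a check of interactions. It closes that paragraph with: "Factors associated with long-term mortality will be evaluated using the same methodology". The list of secondary outcomes contains both all-cause and cardiovascular long-term mortality.

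**The concern.** Three tests are named for the baseline table. Analysis of variance and chi-square both handle any number of groups. Mann–Whitney handles two. For a grouping factor with three levels it cannot answer the question that the sentence asks, namely whether a characteristic differs across the AKIN categories. An analyst who follows the text literally has to run it pair by pair, and without adjustment that produces more chance differences than one overall test would.

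What is at stake is limited. Skewed baseline variables could be reported as differing between AKIN stages more often than they should be, and the parametric and rank-based rows of one table would be testing different hypotheses.

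A second, looser matter of wording is that one sentence sends both mortality outcomes to the method of the main outcome, although only one of the two has a competing event.

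**Working it through.** **No figure to reproduce.** The article states no number that depends on the choice of baseline test. The nearby total of 1200 patients (700 + 150 + 350 = 1200) adds up and is unaffected.

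**Inputs**
- Tests named and entry level: from the article, as quoted.
- Number of AKIN categories: not stated. Three is assumed from the named classification; the choice of analysis of variance fits more than two.
- Significance level for baseline tests: not stated. Two-sided 0.05 is assumed for illustration.
- Total size: 1200. The split across stages is not stated, so three splits were tried.

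**Step 1: pairwise tests if they were independent.** Three groups give 3 pairs. The chance of at least one p < 0.05 under the null is 1 − (1 − 0.05)³ = 1 − 0.857375 = 0.143.

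**Step 2: pairwise tests as they really are.** The three pairs share groups, so the tests are correlated and the true figure is somewhat lower. Simulation used 4000 null data sets per split, with a skewed (lognormal) variable:

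| Group sizes | At least one pairwise Mann–Whitney p < 0.05 | Kruskal–Wallis p < 0.05 |
|---|---|---|
| 400 / 400 / 400 | 12.9% | 5.3% |
| 600 / 300 / 300 | 11.2% | 4.7% |
| 700 / 300 / 200 | 11.2% | 4.4% |

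Together with Step 1 this gives about 11–14% per variable for unadjusted pairwise use, against about 5% for one overall rank test. The simulation error on 4000 runs is about 0.3 percentage points at 5% (√(0.05 × 0.95 / 4000) = 0.0034), so the Kruskal–Wallis results agree with the nominal level.

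**Step 3: does the mortality sentence give a wrong result?** One cohort of 1200 was simulated with one covariate and follow-up of up to 3 years (assumed values, 212 deaths).
- All-cause death, no competing event: Fine–Gray coefficient 0.4734, Cox coefficient 0.4734. The two coincide, because with no competing event the two risk sets are the same.
- Cardiovascular death (83 events) with other death competing (129 events; 83 + 129 = 212): subdistribution coefficient 0.510, cause-specific Cox coefficient 0.541. Here the models differ, so the choice should be stated.

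**The case against.** The strongest defence of the Mann–Whitney wording is that this is a condensed article, that the stages might be merged into two groups or compared in adjusted pairs, and that only descriptive comparisons are affected. The last part stands and fixes the severity as minor. The rest does not remove the point. The article names the test rather than leaving it open, says nothing of merging or adjustment, and pairs it with analysis of variance.

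Three stronger readings are tempting, and the documents do not support them.

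- *That the mortality analysis is wrong, because all-cause death has no competing event, or because CKD would be coded as one and deaths after CKD lost.* The listed outcome includes cardiovascular mortality, for which death from other causes is a real competing event. For all-cause death the model reduces to Cox. Nowhere is CKD coded as competing with death. The only competing risk described is death itself, in the sample-size section. Incident CKD is defined only among patients with recovered function at day 90, so it would not serve the whole cohort. Any count of lost deaths would rest on CKD rates that the article does not give. The reference to the same methodology may also mean the whole screening-to-multivariable sequence.
- *That the AKIN category at inclusion is the category at ICU discharge, when many patients have recovered.* The abstract and the participants section tie AKIN stage to the episode during the ICU stay, and the words may simply say when baseline is described. This is ambiguous wording at most.
- *That baseline p-values would miss their stated level.* The article states no level for them.

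**Conclusion.** The point holds as a minor mismatch between a named test and its grouping factor. Mann–Whitney cannot give an overall comparison across more than two AKIN categories. Under the assumptions of three stages, a 0.05 level and unadjusted pairwise use, about 11–14% of null variables would show at least one false positive, against about 5% with one overall test. If the stages were merged into two groups, or the pairs adjusted, the inflation would disappear, but the article says neither. The main outcome, the score, the eGFR mixed models and the sample size are unaffected. The mortality sentence needs clearer wording only; nothing in it leads to a wrong estimate.

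**What to change.** - In the baseline sentence, replace Mann–Whitney with Kruskal–Wallis for continuous variables compared across AKIN stages.
- As a clarification, state that all-cause mortality is analysed by Cox regression, and cardiovascular mortality by competing-risk analysis with death from other causes as the competing event.

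Both are changes of wording. They need no additional data or patients and no change to the design or sample size.

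### Choosing covariates for the CKD and mortality models by univariate p < 0.10 admits noise, loses real predictors and overstates the evidence for the factors kept; its role in the score is left unclear

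*Protocol article*

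**What the plan says.** All of this is in the Protocol article, in the section on data collection, monitoring and data analysis, unless another section is named.

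- **Determinants of CKD.** "Factors associated with main outcome will be evaluated using a competing risk survival analysis". The rule for entry is that factors with a univariate p "value lower than 0.10 will be included in the multivariate model". Interactions of clinical interest are then examined, with age, gender and preexisting diabetes named. No variable is named as forced in.
- **Mortality.** Factors associated with long-term mortality follow the same method.
- **Score.** A separate paragraph lists four steps. It opens with "1) evaluation of factors associated with the main outcome using competing risk analysis". The second step is "assessment of the selection of the variables using the least absolute shrinkage and selection operator (LASSO) method". The third is evaluation of performance, and the fourth is "assessment of the internal validity using bootstrapping". The paragraph ends by saying: "Such a score will be developed using two-thirds of the entire cohort and validated (external validation) using the remaining one-third".
- **Numbers.** The section Sample size allows for 10% attrition and 20% competing deaths and sets a total of 1200. The largest group is "700 AKI patients who would fully recover kidney function at ICU discharge". The other two groups are 150 whose function is still impaired and 350 who had CKD beforehand.

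**The concern.** The threshold is a stated rule, so this is not detail that a condensed article leaves to the analysis plan. Nothing elsewhere in the article repairs it. Determinants of CKD are a main aim of the study.

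The rule has three faults. A 10% threshold lets through one null candidate in ten. With few events it also rejects many real predictors, and it judges each factor unadjusted, so a predictor masked by its correlation with others is dropped. Finally, the factors kept are tested on the data that chose them, so their p-values and intervals ignore the selection.

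The rule also sits awkwardly with the planned interactions: as written, the main effect of age, gender or diabetes could be screened out while its interaction is still tested.

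The bootstrap and the held-out third are planned only for the score. The determinants and mortality models have no stated protection against selection.

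**Working it through.** **1. The plan's own figure.** 700 + 150 + 350 = 1200, so the parts add up. The 1200 cannot be rebuilt from the article, which states no expected CKD incidence, and the event count below therefore rests on assumptions.

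**2. Inputs.** From the article: threshold 0.10, 700 patients, 10% attrition, 20% competing deaths, two-thirds for development. Assumed here: CKD incidence of 10, 20 or 30%; 20, 30 or 40 candidates that are null and independent; real effects of HR 1.5 or 2.0 for a binary factor with 30% prevalence.

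**3. Events.** At risk: 700 × 0.9 × 0.8 = 504. Development: 504 × 2/3 = 336.

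| Incidence | Events, all 504 | Events, development 336 |
|---|---|---|
| 10% | 50 | 34 |
| 20% | 101 | 67 |
| 30% | 151 | 101 |

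Without removing competing deaths, 700 × 0.9 = 630, and development (420) has 42, 84 or 126 events. The 700 are defined by recovery at ICU discharge but the main outcome by recovery at day 90, so 504 is an approximation.

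**4. Null variables admitted.** The expected number is k × 0.10 and the chance of at least one is 1 − 0.9^k. For k = 20, 30, 40 this gives 2, 3, 4 variables and 88, 96, 99%.

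**5. Real predictors lost.** Chance of failing the screen = 1 − Φ(√(D × 0.3 × 0.7) × ln HR − 1.645), the Schoenfeld approximation with D events. For D = 67 and HR 1.5: √(67 × 0.21) = 3.751; × 0.4055 = 1.521; − 1.645 = −0.124; Φ = 0.45; fails in 55%.

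| D | HR 1.5 fails | HR 2.0 fails |
|---|---|---|
| 35 | 71% | 41% |
| 67 | 55% | 17% |
| 100 | 42% | 6% |

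These D are close to the development-set events. If the determinants model uses all 504 patients, D is about 50, 100 or 150: HR 1.5 then fails in 63, 42 or 26%, and HR 2.0 in 27, 6 or 1%.

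**6. Effect on reported p-values.** A null p-value is uniform. For a null factor independent of the others, the chance of p < 0.05 given that it passed p < 0.10 is about 0.05 / 0.10 = 50%. A reader of the final model would assume 5%.

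**7. Correlated candidates, and the score.** A simulation of 120 runs per incidence used 504 patients split 2:1 and 30 candidates with correlation 0.2. Six were real, with log odds ratios 0.4, 0.4, 0.3, 0.3, −0.3, −0.3 (sum 0.8). A binary outcome stood in for competing-risk data. A candidate's unadjusted covariance with the linear predictor is b × 0.8 + 0.2 × 0.8. That is 0.16 for a null variable and −0.24 + 0.16 = −0.08 for a real effect of −0.3, so the screen favours the null variable. On average 5.3, 6.6 or 8.0 of 24 null variables passed and 2.7, 2.1 or 1.9 of 6 real ones were lost.

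| AUC at incidence | 10% | 20% | 30% |
|---|---|---|---|
| Screen then refit: apparent | 0.752 | 0.719 | 0.715 |
| Screen then refit: true | 0.641 | 0.646 | 0.657 |
| Bootstrap, screened set fixed | 0.693 | 0.667 | 0.666 |
| Bootstrap, screen repeated | 0.654 | 0.647 | 0.655 |
| Held-out third, mean (SD) | 0.642 (0.09) | 0.644 (0.05) | 0.652 (0.05) |
| LASSO on all: apparent | 0.741 | 0.734 | 0.739 |
| LASSO on all: true | 0.626 | 0.647 | 0.664 |
| Screen then LASSO: true | 0.634 | 0.647 | 0.657 |

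With the screened set fixed, the bootstrap is too high by 0.693 − 0.641 = 0.052, 0.667 − 0.646 = 0.021 and 0.666 − 0.657 = 0.009. The bootstrap and held-out rows refer to the screened refit, not to a LASSO fit.

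**The case against.** The strongest objection concerns the score. The p < 0.10 sentence belongs to the determinants paragraph. The score has its own steps, and step 1 mentions no threshold and does not say that only screened variables reach LASSO. The article does not say what the bootstrap repeats; being listed fourth does not mean that selection is left out, and a condensed article may leave that detail to the full plan. A third of the cohort is also held out. All of this stands. A reader might infer that the screen makes the published score look better than it is, but the article does not support that. Apparent performance would be inflated, and so would a bootstrap begun after selection, but the article commits to neither. The held-out estimate was not inflated in the simulation. Screening the whole cohort before the split changed it little (0.657, 0.642, 0.648, against true values of 0.646, 0.647, 0.657).

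Nor is the screen the main source of optimism. LASSO on all candidates had similar apparent optimism and about the same true AUC. Much of it comes from few events per candidate.

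The sizes also depend on incidence, candidate number and effects that the article does not give. That is so for the magnitudes, but not for the direction: a 10% threshold admits null variables and limited events lose real ones under any such choice.

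None of this answers the point on the determinants and mortality models, where the rule is explicit and unprotected.

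**Conclusion.** The concern holds for the multivariate models of CKD and long-term mortality. Under the assumptions listed, 2, 3 or 4 null variables enter on average from 20, 30 or 40 candidates. A real HR of 1.5 is lost in 71, 55 or 42% of studies at development-set event counts, or 63, 42 or 26% if all 504 patients are used. The p-values and intervals of the factors kept are too favourable. The mortality model shares the fault, but its event count was not worked out here.

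For the score, the point is conditional. Step 1 nearly repeats the wording of the screened analysis, so a screen before LASSO is the natural reading, though not an explicit one. If so, the screen is redundant, and a bootstrap started after it would overstate AUC by about 0.05, 0.02 or 0.01. If not, the determinants model and the score may name different predictors, with no stated way to reconcile them. The held-out third is a fair check on average but an imprecise one (SD 0.05 to 0.09, on about 17 to 50 events). Inflated reported performance of the score is not established.

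**What to change.** 1. Delete the p < 0.10 rule for both the CKD and the mortality model.
2. Fit each with a covariate set fixed in advance on clinical grounds, its length limited by the expected number of events. Keep the main effect of any factor whose interaction is tested.
3. State that LASSO is applied to the full pre-specified candidate list, within the development set, with no prior univariate filter.
4. State that every data-driven selection and tuning step is repeated in each bootstrap sample.

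The changes should be fixed before outcome data are analysed. They cost a few sentences and some computing time. Reported internal performance will probably be lower. The gain is sound inference on determinants and honest internal validation; no material gain in true discrimination should be claimed.

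### A held-out third of the study's own cohort is called external validation; it is split-sample validation, and it withholds about a third of the events from building the score

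*Protocol article*

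**What the plan says.** The section on data collection, monitoring and data analysis sets out the score: "The score aiming at predicting the occurrence of CKD at 3 years will be built as follows", followed by four steps. The second is "assessment of the selection of the variables using the least absolute shrinkage and selection operator (LASSO) method" and the fourth is "assessment of the internal validity using bootstrapping". The next sentence adds a data split: "Such a score will be developed using two-thirds of the entire cohort and validated (external validation) using the remaining one-third".

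The recruitment section gives the only source of patients: "Patients will be recruited from 17 ICU (15 in the Greater Paris area, 1 in Clermont-Ferrand and 1 in Amiens", with follow-up in 10 nephrology centres. There is one set of eligibility criteria, one follow-up schedule and one definition of the main outcome. That outcome applies to patients whose eGFR is at least 60 mL/min/1.73 m² at day 90. The article does not say how the third is chosen, and it names no other cohort.

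**The concern.** External validation means testing a finished score in patients who were not part of the study that produced it. A fraction of the same cohort does not meet that description, so the label promises evidence that the stated design does not supply. The score is the aim given in the Background, and the Discussion presents it as a way to find patients for early management. A report that carried the label forward could lead others to use the score in their own hospitals on that strength.

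The split also has a cost. The score is fitted on about two-thirds of the events, and its performance is estimated on the remaining third. The same paragraph already plans bootstrapping, which can estimate optimism without setting any patients aside.

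**Working it through.** **What the article lets us reproduce.** The Sample size section gives "700 AKI patients who would fully recover kidney function at ICU discharge, 150 with impaired kidney function at ICU discharge and 350 with preexisting CKD": 700 + 150 + 350 = 1200, which agrees with the stated total. The article gives no CKD incidence, no target for discrimination and no precision for the validation, so there is no planned figure to check the split against. What follows is an illustration.

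**Inputs from the article**
- Patients recovered at ICU discharge: 700. This is a proxy, because the at-risk set is defined at day 90.
- Losses: "Assuming an attrition bias of 10% and a competing risk of death of 20" per cent.
- Split: two-thirds and one-third.

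**Assumptions, not in the article**
- 3-year CKD incidence of 10, 20 or 30% among evaluable patients.
- A true c-statistic C of 0.75.

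**Step 1, patients.** 700 × 0.9 × 0.8 = 504 evaluable. Development: 504 × 2/3 = 336. Held out: 504 / 3 = 168.

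**Step 2, precision.** Hanley–McNeil standard error, with e events and m non-events:

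SE² = [C(1 − C) + (e − 1)(A − C²) + (m − 1)(B − C²)] / (e·m), where A = C/(2 − C) and B = 2C²/(1 + C).

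At C = 0.75, A = 0.600, B = 0.6429, A − C² = 0.0375, B − C² = 0.0804 and C(1 − C) = 0.1875.

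Worked case at 10% incidence:
- Held-out third: e = 16.8, m = 151.2. SE² = (0.1875 + 0.5925 + 12.070) / 2540.2 = 0.00506, SE = 0.0711, half-width 1.96 × 0.0711 = 0.139.
- All patients: e = 50.4, m = 453.6. SE² = (0.1875 + 1.8525 + 36.370) / 22861 = 0.00168, SE = 0.0410, half-width 0.080.

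**Step 3, results for 504 evaluable patients**

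| Assumed incidence | Events, all | Events, development | Events, held out | 95% half-width, held out | 95% half-width, all |
|---|---|---|---|---|---|
| 10% | 50 | 34 | 17 | 0.139 | 0.080 |
| 20% | 101 | 67 | 34 | 0.102 | 0.059 |
| 30% | 151 | 101 | 50 | 0.086 | 0.050 |

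At 10% incidence the held-out interval runs from about 0.61 to 0.89, against about 0.67 to 0.83 with all patients.

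**Step 4, how far this depends on the base.** If all 700 were evaluable, the held-out third would have 23, 47 or 70 events and half-widths of 0.118, 0.086 or 0.073, against 0.068, 0.050 or 0.042. The ratio stays close to √3 = 1.73 throughout, because a third of the patients carries a third of the information. Using all patients gives 504 / 336 = 1.5 times the expected events for model building, whatever the incidence.

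**Limits of the method.** Hanley–McNeil treats the outcome as binary. It ignores censoring, and removing deaths from the base is a simplification of the planned competing-risk analysis. The all-patient half-width also leaves out the extra variability of an optimism correction. The ratio is firmer than the absolute widths.

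**The case against.** - **The split mechanism is not given.** This is a condensed article, and the full protocol may split by centre or period, which would be a geographic or temporal check. That stands: a reader might infer that both parts come from the same ICUs over the same period, and the article does not establish this. Yet it makes a positive claim of external validation and states no such split. A split by centre or period would still share eligibility, follow-up and outcome definition, and would still withhold events.
- **A hold-out is inefficient but not invalid.** It gives an honest estimate for the score fitted on the development part, bootstrapping is planned as well, and nothing forbids a later refit on everyone. That stands too, so the hold-out should not be read as producing biased performance. But a refit is not stated, and if it were done, the held-out result would describe a different model from the one published.
- **The score would hardly improve.** A reader might infer that the split makes it clearly less accurate. An illustrative simulation with a ridge-penalised logistic score put the gain from using all patients at only 0.007 to 0.010 in the c-statistic. That is not the planned competing-risk LASSO score, so it indicates no more than order of magnitude, and the order is small.
- **The rest of the study is unaffected.** The main outcome, CKD incidence, does not depend on the split; nor do the sample size and data collection. Agreed: the point concerns the score only.

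**Conclusion.** The point holds in two parts. First, on the text as it stands, the held-out third is internal, split-sample validation. The label external is wrong unless an independent cohort is involved, and none is named. Second, the split withholds an expected one-third of the events from model building and yields a validation interval about 1.7 times wider than use of all the data.

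The relative figures need no assumed incidence. The absolute ones (half-widths of about 0.14, 0.10 and 0.09 against 0.08, 0.06 and 0.05) rest on 504 evaluable patients, recovery at ICU discharge standing in for day 90, the assumed incidences and a c-statistic of 0.75. At 10% incidence the held-out estimate would hardly separate a weak score from a strong one; at 20 to 30% the loss is milder.

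**What to change.** Delete the two-thirds/one-third split and the term external validation. In their place:
- Fit the score on all at-risk patients.
- Report bootstrap optimism-corrected discrimination and calibration, repeating the whole selection procedure, LASSO included, in each resample.
- Examine transportability by internal-external cross-validation over groups of ICUs. Single ICUs are too small: on the figures above, 50, 101 or 151 events over 17 ICUs is about 3, 6 or 9 each if recruitment is even.
- State that external validation requires an independent cohort.

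This costs some analysis time and the loss of the label. It needs no new patients, visits or data, and can be settled before the analysis.
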